### Randomization and allocation

Initially all provinces of Iran were categorized to five stratum based on their geographic location (North, East, West, South, and Center of Iran) and one province in each stratum were randomly selected; then, the list of the cities located in each province were provided. Since the socioeconomic status in the center of provinces may differ from other cities, in the second phase, all cities in each province were classified in two clusters of center of the province and other cities. At the end, four cities were randomly selected from the list of other cities in each province.

For allocation of protocols, in the cluster of the provincial centers, five different protocols were randomly allocated to each provincial center. Also, in the cluster of other cities, four other cities in each province were randomly allocated to the rest of the protocols (Fig. 1). Sample size for each city was estimated through probability proportional to size (PPS), defined by number of live births of the cities.

**Fig. 1 Fig1:**
[figure not shown]
Randomization and allocation of study

### Intervention

Following the approval of this study, the study procedure was released as a guideline to all the selected cities. In this respect, workshops were conducted in each city to introduce the study protocol and train the caregivers and study staff accordingly. Dieticians, obstetricians, internal medics, laboratory technicians and endocrinologists in each province were invited to a scientific workshop to harmonize and coordinate the follow ups and treatment of GDM patients. Scientific teams with specialists and executive members conducted visits every 2 months. A telegram channel was developed for daily online communication of scientific members and executive members at both provincial and city levels to answer questions and solve any problems encountered.

Along with routine standard prenatal care, all pregnant women was screened for GDM based on the pre-specified protocol assigned to each city. In this respect, early screening of GDM was conducted in the first trimester of pregnancy, using fasting plasma glucose (FPG) from venous sample with the specific threshold based on each screening protocol; based on the results of those screening tests, pregnant women were classified in to three groups: (i) diagnosed with preexisting pre-gestational overt diabetes; (ii) gestational diabetes and (iii) non-GDM women. In addition, at 24–28 weeks of gestation, those not previously known to have diabetes (overt or gestational), were screened again for GDM based on pre-specified protocol criteria assigned to that city. All study participants were followed till delivery and pregnancy and neonatal outcomes and health cost were recorded in detail. Definitions of various protocols for screening are presented in Table 1.

**Table 1 Tab1:** Definitions of various protocols for screening of gestational diabetes mellitus

Protocol	First trimester	Second trimester		
	Diagnostic criteria for GDM	Method for GDM screening	Diagnostic threshold of test	Diagnostic criteria
A	92 mg/dL < FPG > 126 mg/dL	One step with 2-h 75 g OGTT	Fasting ≥ 92 mg/dL 1 h ≥ 180 mg/dL 2 h ≥ 153 mg/dL	GDM is defined as any of the given plasma glucose values are met or exceeded
B	100 mg/dL < FPG > 126 mg/dL	One step with 2-h 75 g OGTT	Fasting ≥ 92 mg/dL 1 h ≥ 180 mg/dL 2 h ≥ 153 mg/dL	GDM is defined as two or more of the given plasma glucose values are met or exceeded
C	100 mg/dL < FPG > 126 mg/dL	One step with 2-h 75 g OGTT	Fasting ≥ 92 mg/dL 1 h ≥ 180 mg/dL 2 h ≥ 153 mg/dL	GDM is defined as any of the given plasma glucose values are met or exceeded
D	92 mg/dL < FPG > 126 mg/dL	Two steps with 50 g GCT—1 h following 3-h 100 g OGTT	50 g GCT:	GDM is defined as if two or more of the given plasma glucose values in 100 g OGTT are met or exceeded
			BS-1 h: ≥ 140 mg	
			100 g OGTT:	
			Fasting ≥ 95 mg/dL	
			1 h ≥ 180 mg/dL	
			2 h ≥ 155 mg/dL	
			3 h ≥ 140 mg/dL	
E	100 mg/dL < FPG > 126 mg/dL	Two steps with 50 g GCT—1 h following 3-h 100 g OGTT	50 g GCT:	GDM is defined as if two or more of the given plasma glucose values in 100 g OGTT are met or exceeded
			BS-1 h: ≥ 140 mg	
			100 g OGTT:	
			Fasting ≥ 95 mg/dL	
			1 h ≥ 180 mg/dL	
			2 h ≥ 155 mg/dL	
			3 h ≥ 140 mg/dL	

In the first trimester overt diabetes is defined as FPG ≥ 126 mg/dL

*FPG* fasting plasma glucose, *GCT* glucose challenge test, *OGTT* oral glucose tolerance test

Each group received packages of standard care based on their health status. In this respect, non-GDM pregnant women received routine standard care recommended by the American College of Obstetricians and Gynecologists (ACOG) 2013 [41]. Moreover, pregnant diabetic patients received specific prenatal and diabetic care, recommended by the American College of Obstetricians and Gynecologists (ACOG) 2013 [43] and the American Diabetes Association (ADA) 2016 [44].

### Summary of management of Gestational Diabetes in Pregnancy

After diagnosis of GDM, treatment was initiated with medical nutrition therapy, physical activity, and weight management and blood glucose monitoring to achieve the targets recommended by ADA guideline 2016 [44] including fasting, 95 mg/dL, 1-h postprandial, 140 mg/dL or 2-h postprandial, 120 mg/dL. Medical nutrition therapy for GDM will be individually planed for participants by the dietitian. The food plan provides enough calorie intake to promote fetal/neonatal and maternal health, achieve glycemic goals, and promote appropriate gestational weight gain, based on the Dietary Reference Intakes (DRI) recommendation including a minimum of 175 g carbohydrate, a minimum of 71 g protein, and 28 g fiber [44].

If women did not achieve glycemic goals within 2 weeks, pharmacologic therapy will be offered by specialized physicians including obstetricians, internists or endocrinologists at the second level of the healthcare delivery system. Insulin is the first-line agent recommended for treatment of GDM. Self-monitoring of blood glucose (SMBG) was used for achieving and maintaining therapeutic goals in insulin-treated patients. The frequent use of capillary blood glucose tests of SMBG was scheduled four times a day, fasting, 2-h after breakfast, lunch and dinner or if the patients had hypoglycemic symptoms for at least 2 weeks. After achieving the therapeutic target, SMBG was performed two times a day. In addition, if women decline insulin therapy, metformin will be offered as an alternative or adjunct to insulin after clarifying the harms and benefits of metformin therapy for patients [44] (Fig. 2).

**Fig. 2 Fig2:**
[figure not shown]
Flow chart of screening and management of Gestational Diabetes in Pregnancy. *GDM: gestational diabetes mellitus; **FPG: fasting plasma glucose

### Data collection

Data were collected from participants at scheduled time points (Table 2) using pre-specified questionnaires and clinical and para clinical exams by trained midwives. Moreover, data on neonatal mortalities that occurred after hospital discharge were collected at 4 weeks post-partum by telephone and subsequent reviews of medical records.

**Table 2 Tab2:** Outlines of periodic assessments of study participants

	Method or sample used	> 14 week	14–19 week	20–23 week	24–30 week	31–34 week	35–37 week	38 week	39 week	40 week	Birth	28 days after birth
Maternal^a,b^												
Past medical, reproductive and obstetrics history												
Weight	Calibrated scale	^a^	^a^	^a^	^a^	^a^	^a^	^a^	^a^	^a^		
Height	Stadiometer	^a^										
Blood pressure (systolic, diastolic)	Calibrated mercury sphygmomanometer	^a^	^a^	^a^	^a^	^a^	^a^	^a^	^a^	^a^		
Fundal height	Measuring tape		^a^	^a^	^a^	^a^	^a^	^a^	^a^	^a^		
Fetal heart rate			^a^	^a^	^a^	^a^	^a^	^a^	^a^	^a^		
Fetal ultrasound		^a^			^a^		^a^					
FPG	Venous sample	^a^										
OGTT-75 g or GCT following OGTT-100 g	Venous sample				^a^							
Quality of life	Questionnaire		^a^	^a^	^a^	^a^		^a^				
Drug adherence	Questionnaire		^a^	^a^	^a^	^a^		^a^				
GDM treatment satisfaction	Questionnaire		^a^	^a^	^a^	^a^		^a^				
Cost-effectiveness	Questionnaire		^a^	^a^	^a^	^a^		^a^			^a^	
Feto-maternal outcomes^c^											^a^	
Neonatal^a,b^												
C-peptide	Cord sample										^a^	
Weight	Calibrated baby scale										^a^	
Recumbent length	Infantometer										^a^	
Head circumference	Measuring tape										^a^	
Blood glucose^e^	Heel-stick sample										^a^	
Neonatal outcomes^d^											^a^	^a^

^a^Data collected from routine and expert scans that occur during the time points

^b^If GDM or other complication were diagnosed, subsequent additional visits, measurements and standard treatment were performed

^c^Feto-maternal outcomes continuously recoded include abortion, gestational hypertension, pre-eclampsia/eclampsia, preterm birth, instrumental delivery, primary cesarean section, polyhydramnios, oligohydramnios, premature rupture of membrane, placenta Previa, placenta abruption, postpartum hemorrhage, wound and incision infection

^d^Neonatal outcomes include shoulder dystocia, intrauterine growth restriction, macrosomia, Apgar score, neonatal hypoglycemia, neonatal hypocalcemia, neonatal hyperbilirubinemia, polycythemia, neonatal intensive care unit admission, neonatal care unit admission, Respiratory distress syndrome, congenital anomaly, neonatal asphyxia, intrauterine fetal death, perinatal death, Erb–Duchenne palsy, birth trauma, neonatal sepsis

^e^Measured for high risk groups

### Questionnaires

*Prenatal questionnaire* This comprehensive questionnaire includes two sections: 1—contains the past medical, reproductive, obstetrics, and gynecological history, completed only at first prenatal visit 2—focuses on current pregnancy information and this part was completed at each prenatal visit during pregnancy (Additional file 1: PART 1: Prenatal Care Form).*Delivery, postpartum and neonatal questionnaire* This questionnaire contains the details of delivery and its methods and any adverse maternal–fetal/neonatal outcomes (Additional file 1: PART 2. Childbirth and New-born Report Form).*Quality of life questionnaire* The Iranian version of 36-item short form health survey questionnaire (SF-36) [45–48] was used to measure the physical and mental components of health-related quality of life. The SF-36 included 36 items with 8 subscales; physical functioning, role limitations due to physical problems, bodily pain, general health perceptions, vitality, social functioning, role limitations due to emotional problems and perceived mental health. This questionnaire was completed monthly for all GDM patients since the time of diagnosis. Also, it were done for 5% of non-GDM pregnant women visited from the first visit for prenatal care (Additional file 1: PART 3. 36-Item Short Form Survey Instrument).*Cost-effectiveness questionnaire* This questionnaire included 50 items with three subscales: (i) self-purchased health care, (ii) travel costs for making return visit(s) to health care and (iii) time costs of travelling and attending health care center. Effectiveness was measured in terms of quality adjusted life years (QALYs), using the EQ-5D 3L questionnaire completed by participants at the follow up time points. It includes five questions, each assessing one of five dimensions of the health related quality of life (Mobility, Self-Care, Usual Activities, Pain/Discomfort and Anxiety/Depression). Each of these dimensions has to be answered on a 3-level scale (no problems, some or moderate problems, and extreme problems). The scales are scored from 1 (no problem) to 3 (extreme problem) in each question; and finally the score digits are placed together to yield a 5-digit code for the health status of each patient (Additional file 1: PART 4. Cost effectiveness Form).

The need for other assessments, such as serum bilirubin or imaging tests were determined based on clinical indications.


### Data cleaning and missing data

The following minimal data must be available for women to be included in the analysis of pregnancy outcomes: Completed enrollment forms and questionnaire, completed results of GDM screening, type of delivery, birth weights and clear status of exclusionary criteria.

Missing values will be managed using appropriate imputation methods. Outliers will be identified using graphical tools including boxplot and/or Model-based methods like Chauvenet’s criterion and Dixon’s Q test [62, 63].

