### Cost-effectiveness analysis (CEA)

A cost-effectiveness analysis, comparing 4 less intensive screening strategies with IADPSG criteria will be conducted on an intention-to-treat basis by estimating various parameters including Quality-adjusted life years (QALYs), incremental cost-effectiveness ratio (ICER), and incremental net benefit (INB). To estimate mean cost in each treatment group, regression models will be used. General linear models (GLM) with appropriate variance functions e.g. gamma, Poisson, etc. and link will be used to identify the relationship between treatment allocation and costs after adjusting for minimization and the appropriate prognostic covariates at baseline (e.g. Baseline EQ-5D score). To estimate the incremental effect of the treatment indicator variable, recycled predictions will be used [64].

A sensitivity analysis will be conducted to assess how sensitive the cost-effectiveness results are to variation in key parameters including cost.

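### The pregnancy-outcome analysis admits only women with completed GDM screening, which conditions on adherence to the allocated strategy after allocation

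*Protocol article*

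**What the plan says.** Under Data cleaning and missing data, the protocol article sets an entry condition: "The following minimal data must be available for women to be included in the analysis of pregnancy outcomes". The items that the article then names are "Completed enrollment forms and questionnaire, completed results of GDM screening, type of delivery, birth weights and clear status of exclusionary criteria". The next paragraph adds "Missing values will be managed using appropriate imputation methods".

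Under Research questions and objectives, the primary outcomes are birth weight above the 90th percentile and primary caesarean section. Both are pregnancy outcomes, so the rule defines the primary analysis set.

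Under Randomization and allocation, the unit of allocation is the city; for the provincial centres, "five different protocols were randomly allocated to each provincial center". Screening comes later, under Intervention: a fasting glucose in the first trimester, and at 24–28 weeks women without an earlier diagnosis "were screened again for GDM based on pre-specified protocol criteria assigned to that city". In Table 1, protocols A, B and C use a single 2-hour 75 g OGTT in the second trimester. Protocols D and E use a 50 g GCT and then a 3-hour 100 g OGTT, with the diagnosis resting on the latter: "GDM is defined as if two or more of the given plasma glucose values in 100 g OGTT are met or exceeded".

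An intention-to-treat basis is stated once, for the economic evaluation: "A cost-effectiveness analysis, comparing 4 less intensive screening strategies with IADPSG criteria will be conducted on an intention-to-treat basis".

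**The concern.** The screening strategy is the intervention. Whether a woman completes it is an event that follows allocation and is shaped by what was allocated. A set restricted to completers compares the strategies only among women in whom they were carried out, and the groups so formed are no longer the groups that were randomised.

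Two features make this more than a formality.

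- **Completion means different things across arms.** In D and E, a woman who passes the GCT threshold and never has the 100 g test has probably not completed screening. She has been selected on a raised glucose value and has no diagnosis. In A to C, a woman who misses the 75 g OGTT has not been selected on any glucose value from that phase.
- **Timing.** Read literally, the rule also drops women without a first-trimester diagnosis who deliver or lose the pregnancy before the 24–28 week test. Yet the article defines preterm birth from 20 weeks and lists preterm labour and intrauterine fetal death as secondary outcomes. Some of the events it intends to count could not enter the analysis.

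At stake is the population behind both primary non-inferiority conclusions. In a non-inferiority trial, a completer set as the only stated population is a weak basis for the claim.

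**Working it through.** The article gives no completion rates, so there is no stated figure to reproduce. The check has two parts: what the rule does, and how large its effect could be under labelled assumptions.

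**What the rule does**

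1. Allocation is to cities, before any enrolled woman is screened (Randomization and allocation).
2. Screening has two phases, both after allocation (Intervention).
3. Second-phase completion requires one test in A–C and, for GCT-positive women, two tests in D–E (Table 1).
4. A woman diagnosed in the first trimester needs no second test. That share depends on the fasting threshold: 92 mg/dL in A and D, 100 mg/dL in B, C and E. So who can be incomplete also varies with the protocol.
5. The entry condition uses this completion status, so it conditions on a post-allocation variable that depends on the arm.

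**Possible size**

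From the article (Sample size calculation): event rate 10% in all groups, margin 0.03. Assumed: 20–30% of a two-step arm is GCT-positive and 10–20% of those do not return. The excluded share e is then 0.20 × 0.10 = 2% to 0.30 × 0.20 = 6%. Also assumed: an excess risk of 5–10 points among the excluded, and no exclusion effect in arm A.

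If the excess is measured against completers, understatement = e × excess:

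- 0.02 × 0.05 = 0.001, or 0.1 points, 3% of the margin
- 0.06 × 0.10 = 0.006, or 0.6 points, 20% of the margin

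If it is measured against the whole arm, with event rate r among the excluded, the observed rate is (0.10 − e·r)/(1 − e):

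| e | r | observed rate | shift (points) | share of margin |
|---|---|---|---|---|
| 2% | 15% | 9.90% | −0.10 | 3% |
| 6% | 20% | 9.36% | −0.64 | 21% |
| 5% | 20% | 9.47% | −0.53 | 18% |
| 5% | 30% | 8.95% | −1.05 | 35% |
| 15% | 30% | 6.47% | −3.53 | 118% |
| any | 10% | 10.00% | 0 | 0% |

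The two conventions agree closely. The last two rows show the ends: a large, high-risk exclusion would exceed the whole margin, and an exclusion at average risk does nothing.

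**Direction**

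Suppose the true rate is 10% in both arms, D loses 2% and A loses 5%, each with r = 20%. D is then observed at 9.80% and A at 9.47%. D looks about 0.3 points worse, so the bias runs against non-inferiority. With the losses swapped, the sign reverses.

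**The case against.** The strongest case on the other side has four parts.

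**The direction is not shown.** A reader might infer that the rule always favours the two-step protocols. The documents do not support that. In A, every woman without an early diagnosis must complete a 75 g OGTT, whereas in D and E only GCT-positive women need the long test. Overall non-completion could be higher in A. B and C, two of the four comparators, use the same second-phase test as A. This objection stands.

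**The economic analysis is not affected as it might appear.** A reader might infer that completer effects and intention-to-treat costs meet in one ICER. They do not: the cost-effectiveness section puts QALYs, ICER and incremental net benefit together on the intention-to-treat basis, and the entry rule is confined to pregnancy outcomes. Only the number needed to treat and the cost per primary outcome prevented, both among the hypotheses, could be drawn from the restricted set. This also stands.

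**The imputation sentence is not a contradiction.** A reader might set it against the requirement for birth weight and delivery type, but it can apply to covariates, secondary outcomes and questionnaires in women who are included. Likewise, the intention-to-treat statement concerns a different analysis.

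**Exclusion of the GCT-positive non-returner is an inference.** The article does not define a completed result or say how she is classified. Exclusion is the likely reading, since her diagnosis depends on a test she did not have, but it is not stated.

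None of this removes the central point. The rule is stated rather than left open, it acts after allocation, and an arm-dependent exclusion of either sign disturbs the randomised comparison.

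**Conclusion.** The concern holds in a limited form. As written, the rule makes both primary comparisons conditional on completing the allocated screening, and the article states no all-enrolled analysis of pregnancy outcomes beside it. This can bias the non-inferiority comparison; that it does so in favour of the two-step protocols is plausible but not established.

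The size cannot be determined from the documents. Under the assumptions of 2–6% excluded from a two-step arm, a 5–10 point excess risk and no exclusion effect in arm A, it is about 0.1–0.6 points, or 3–20% of the 3-point margin. It would be nil if the excluded women carry average risk, and larger if exclusions are more frequent or at higher risk. The case for change rests on the rule itself more than on these figures.

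**What to change.** - Delete completed GDM screening as a condition for the primary analysis set.
- Analyse all eligible enrolled women, in the protocol allocated to their city, whose pregnancy reached a stage at which the outcome is defined. The limit is needed because women enrol before 14 weeks and abortions before 20 weeks are recorded; imputing a birth weight for those pregnancies would be meaningless. Report earlier losses by arm.
- Where birth weight or delivery type is truly missing, impute within protocol using baseline data.
- Keep the current set as a supporting per-protocol analysis, and require both sets to agree before claiming non-inferiority.
- Use the same all-enrolled set for the number needed to treat and for the cost per primary outcome prevented.
- Report screening completion by arm and by step, so that the size of the exclusion can be seen.

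The cost is revised analysis-set wording and one extra analysis run, plus reliance on an imputation model for missing outcomes. No new data should be needed, since the Intervention section says that all participants were followed to delivery with outcomes recorded.

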### Data analysis

To illustrate distribution of the data, appropriate descriptive statistics such as measures of central tendency, index of dispersion and percentiles will be reported along with normality assumption testing through Kolmogorov-Smirnoff test. Maternal, neonatal and obstetric outcomes of the 4 less intensive screening strategies with IADPSG criteria will be compared using parametric or non-parametric statistical tests, where applicable.

In addition, based on the type of outcome variables, Generalized Linear Models (GLMs) with different link function such as linear, count or binary will be applied. Stepwise method with P-value < 0.2 will be used to identify significant confounding variables and estimate adjusted measures of interests. Moreover, longitudinal modeling through Generalized Estimating Equation (GEE) analysis approach will be conducted and to calculate Number Needed to Treat (NNT), the Linear GLM model will be applied as well. Since this is a cluster randomized trial, cluster effect in analysis will be considered.

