**Methods:**

This study is a randomized community non-inferiority trial among 30,000 pregnant women in five different geographic regions of Iran, who were randomly assigned to one of the five GDM screening methods. All first trimester pregnant women, seeking prenatal care in governmental health care systems, who met our eligibility criteria were enrolled. The criteria suggested by the International-Association-of-Diabetes-in-Pregnancy-Study-Group, the most intensive approach, were used as reference. We used the non-inferiority approach to compare less intensive strategies to the reference one. Along with routine prenatal standard care, all participants were scheduled to have two phases of GDM screening in first and second-trimester of pregnancy, based on five different pre-specified protocols. The screening protocol included fasting plasma glucose in the first trimester and either a one step or a two-step screening method in the second trimester of pregnancy. Pregnant women were classified in three groups based on the results: diagnosed with preexisting pre-gestational overt diabetes; gestational diabetes and non-GDM women. Each group received packages for standard-care and all participants were followed till delivery; pregnancy outcomes, quality of life and cost of health care were recorded in detail using specific standardized questionnaires. Primary outcomes were defined as % birth-weight > 90th percentile and primary cesarean section. In addition, we assessed the direct health care direct and indirect costs.

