## Materials and methods

### Research questions and objectives

This study is being performed to provide real data collected from an unbiased population trial for assessment of the following hypothesis: (i) the prevalence of GDM when using the less intensive GDM screening strategies is not more than obtained using the IADPSG criteria. (ii) The pre-specified primary outcomes in less intensive GDM screening strategies are not worse than those obtained using IADPSG criteria. (iv) The cost of health care using less intensive GDM screening strategies is not higher than incurred using IADPSG criteria. (v) The numbers needed to treat (NNT) to prevent one primary outcome in less intensive strategies are the same as those obtained using IADPSG criteria.

The cost of prevention for one primary outcome in less intensive strategies is the same as that for IADPSG criteria.

According to our research hypothesis, primary outcomes hence are: percentage of birth weight > 90th percentile and primary cesarean section. Secondary outcomes are prevalence of neonatal hypoglycemia, birth weight < 10th percentile, neonatal admission to the intensive care unit, shoulder dystocia and birth trauma including fracture of clavicle and brachial plexus injury, intrauterine fetal death, preeclampsia and preterm labor, neonatal hyperbilirubinemia and hypocalcemia. In addition, the study will assess the direct health care costs including prenatal clinic visits, obstetrician visits, endocrinologist visits, dietician visits, blood glucose monitoring equipment, laboratory test cost, pharmacotherapy, additional fetal well-being assessments and hospitalization as well as indirect cost of productivity loss and charges to the family including traveling, food substitution, mother time off paid work, and partner time off work.

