### Sample size calculation

Based on previous studies, we assumed that the primary event rate of macrosomia to be equal to 10% for all groups with no difference. To obtain a statistical power of 85% with a 1-sided type one error of 0.005 (considering multiple comparisons) approximately 4700 patients per group are needed to show the non-inferiority of more intensive compared to lower intensive strategies with a marginal difference of 0.03. With a design effect of 0.001 (for cluster sampling) and loss to follow-up of 11%, sample size reached to 5200 in each group [42].

In addition, superiority analyses will be designed to show that one screening strategy is superior to another after non-inferiority has been demonstrated.

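### The non-inferiority hypotheses are misdirected or incomplete as written: the sizing reverses the direction, primary cesarean has no criterion, and the NNT equality cannot be tested in this design

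*Protocol article*

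**What the plan says.** **Direction.** The abstract (Methods) states: "We used the non-inferiority approach to compare less intensive strategies to the reference one". Hypothesis (ii) under Research questions and objectives agrees: "The pre-specified primary outcomes in less intensive GDM screening strategies are not worse than those obtained using IADPSG criteria". The Sample size calculation section instead sizes the trial "to show the non-inferiority of more intensive compared to lower intensive strategies with a marginal difference of 0.03".

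**Outcomes covered.** The abstract and the objectives name two primary outcomes: birth weight above the 90th percentile, and primary cesarean section. The sizing takes "the primary event rate of macrosomia to be equal to 10% for all groups with no difference", with 85% power and a one-sided error of 0.005. It gives no rate, margin or power for primary cesarean. Definition of study outcomes limits that outcome to women with no previous cesarean.

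**Equality hypotheses.** Hypothesis (v) reads: "The numbers needed to treat (NNT) to prevent one primary outcome in less intensive strategies are the same as those obtained using IADPSG criteria". The sentence after it makes the same claim for the cost of preventing one primary outcome. Overall study design and Intervention describe five arms, all screened.

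**Analysis.** Under Data analysis, the four less intensive strategies and the IADPSG criteria "will be compared using parametric or non-parametric statistical tests, where applicable". The section then adds GLMs with several links, GEE, a linear GLM for the NNT, and allowance for the cluster effect. It does not mention the margin, a confidence limit or non-inferiority.

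**The concern.** In a one-sided non-inferiority test the direction is the null hypothesis. If the direction is reversed, a successful test answers a different question from the one the trial is meant to settle for national policy.

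Hypothesis (ii) covers both primary outcomes, so a protocol can be called not worse only if both have a criterion. One has none, and the quoted 85% power does not apply to it. A margin chosen once results are known would carry little weight.

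An equality hypothesis cannot be established without a stated tolerance. An NNT for protocol A itself also needs an event rate without screening or treatment, which no arm supplies.

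**Working it through.** **1. Direction.** Let p_L be the event rate under a less intensive protocol and p_A the rate under IADPSG.
- Abstract and hypothesis (ii): reject H0: p_L − p_A ≥ 0.03.
- Sample size section: reject H0: p_A − p_L ≥ 0.03.

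Suppose p_A = 10% and p_L = 13%. The first null is true and should stand. For the second, p_A − p_L = −0.03, far below +0.03, so the test would readily succeed although the less intensive protocol is worse by the full margin. With 10% assumed in every group, the sample size formula is the same either way, so the reversal changes no number.

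**2. The plan's own figure.** n per group = [p1(1−p1) + p2(1−p2)] (z0.995 + z0.85)² / margin² = 0.18 × (2.576 + 1.036)² / 0.0009 ≈ 2,610. The document states about 4,700, which this formula does not reproduce. The last step does reproduce approximately: 4,700 × 1.11 = 5,217, or 4,700 / 0.89 = 5,281, against 5,200. That gap is a separate matter, and the point here does not depend on it.

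**3. Primary cesarean, illustration only.** The documents give no cesarean rate, so 20%, 30% and 40% are assumed. The 0.03 margin is borrowed from macrosomia, with one-sided 0.005 as stated.

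*No clustering, 4,700 per group.* Power = Φ(0.03 / √(2p(1−p)/4,700) − 2.576).
- 20%: SE 0.00825, power about 86%
- 30%: SE 0.00945, power about 73%
- 40%: SE 0.01011, power about 65%

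The same formula for n gives 4,640, 6,090 and 6,960 per group for 85% power.

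*With clustering.* The stated 0.001 is read as an ICC (assumption), with five equal cities per arm (assumption; the plan allocates in proportion to live births).
- Evaluable women per arm: 5,200 × 0.89 = 4,628
- Women per city: 4,628 / 5 ≈ 926
- Design effect: 1 + 925 × 0.001 ≈ 1.925
- Effective n: 4,628 / 1.925 ≈ 2,405

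| Outcome and rate | SE = √(2p(1−p)/2,405) | Power |
|---|---|---|
| Macrosomia, 10% (stated) | 0.00865 | 81% |
| Cesarean, 20% (assumed) | 0.0115 | 51% |
| Cesarean, 30% (assumed) | 0.0132 | 38% |
| Cesarean, 40% (assumed) | 0.0141 | 33% |

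Neither set removes women with a previous cesarean. If a quarter had one (assumption), the clustered cesarean powers fall to about 43%, 32% and 27%. If the abstract's 30,000 women (6,000 per arm) are used with 11% loss, they are about 55%, 41% and 35% before that restriction. Power to meet both criteria cannot exceed the cesarean figure.

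**4. NNT.** The NNT of protocol k is 1/(p_0 − p_k), where p_0 is the event rate without screening or treatment. No arm observes p_0, so A's own NNT has no randomised comparator. A between-protocol NNT, 1/(p_L − p_A), is one quantity rather than two that could be the same, and it is undefined at the planned rates: 1/(0.10 − 0.10). No tolerance for equality is given.

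**5. Analysis.** An identity-link (linear) GLM estimates a risk difference, which is the scale of the 0.03 margin. The planned tools can therefore supply the needed estimate; what the section lacks is the link from that estimate to the margin.

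**The case against.** A reader might infer that the plan will run ordinary tests of difference and treat a non-significant result as not worse, so that it cannot deliver a non-inferiority answer. The documents do not support this. The analysis sentence names no test, null hypothesis, level or link, and it covers all maternal, neonatal and obstetric outcomes. The abstract and the sizing set a non-inferiority frame with a margin and a one-sided error, and superiority is to follow only once non-inferiority is shown. A linear GLM and allowance for clustering are planned. The decision rule may also sit in an analysis plan that is not shown. This objection stands, and it reduces the analysis limb to a missing link.

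The reversed direction could be called a slip of wording. It has no effect on the sample size, but the sentence still states the wrong null and contradicts two other sections.

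A condensed article may omit detail. Here, however, the sample size section is present and specific, and it covers one of two primary outcomes.

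The cesarean powers rest on assumed rates, a borrowed margin and a reinterpreted 0.001. That is correct; they are illustrations. The undefined NNT at equal rates likewise reflects a planning assumption, not an expected result. The missing comparator does not depend on it.

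**Conclusion.** The point holds in limited form. Three parts rest on the document's own text: the direction in the sizing contradicts the abstract and hypothesis (ii); primary cesarean has no rate, margin or power, so half of hypothesis (ii) has no criterion; and the NNT and cost-per-prevented-outcome equality hypotheses lack both a comparator for protocol A and a definition of equality. The fourth, the missing tie between the analysis and the 0.03 margin, is under-specification and not a demonstrated error.

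The only size that can be attached is illustrative. With the macrosomia margin borrowed, cesarean power over assumed rates of 20% to 40% runs from about 86% down to 65% without clustering, and from about 51% down to 33% with 0.001 as an ICC and five equal cities. Under those clustered assumptions macrosomia has about 81%. The documents do not support a claim that the sample size is wrong because of the reversed direction.

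**What to change.** - **Sample size calculation:** reword the direction so that less intensive strategies are shown non-inferior to IADPSG. This is a wording change and alters no number.
- **Data analysis:** state that each less intensive protocol is declared non-inferior only if the upper one-sided 99.5% confidence limit of the cluster-adjusted risk difference (less intensive minus A) is below the margin. This uses the linear model and the cluster adjustment already planned.
- **Primary cesarean:** before outcome data by arm are examined, either state a risk-difference margin with the power that results among women without a previous cesarean, or make the outcome key secondary. Recruitment ended in January 2019, so either step must be labelled as a post-recruitment change. The power to be reported is likely to be unfavourable.
- **Hypothesis (v) and the cost-per-prevented-outcome hypothesis:** replace them by the between-protocol risk difference with its confidence interval and the incremental net benefit already planned under Cost-effectiveness analysis.

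No new data are needed. The cost is a dated amendment and, for cesarean, openness about when the criterion was set.
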